### 5.3 Treatment of subjects

Anti-IL-20 (109-0012) 100 mg/vial or Placebo (109-0012) 0 mg/mL will be administered subcutaneously into the abdomen using a standard syringe. The active doses will range from 0.01 mg/kg to 3 mg/kg in the SD phase and from 0.05 mg/kg to 2 mg/kg in the MD phase. The maximum dose of 3 mg/kg has been chosen due to injection volume limitations. The dose to be investigated in the MD expansion phase will be the maximum tolerated dose reached in the previous phases and will not commence until the SD and MD dose-escalation phases have been

completed. For more details see [Table 5–1](#), which presents the anticipated dosing schedule for the different dose cohorts for the SD and MD dose-escalation phases.

The freeze dried drug product will be dissolved in Water for Injection at a concentration of 100 mg/mL and further diluted with the placebo formulation to 10 or 1 mg/mL for the lowest doses. The volume of each injection will not exceed 1.2 mL. The placebo formulation will be provided as a liquid formulation and will have an identical appearance as the reconstituted freeze dried active drug at the lowest doses. At the higher doses the reconstituted active drug solution might differ in colour due to high protein content.

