**Trial products:**

The active drug product, Anti-IL-20 (109-0012) 100 mg/vial, will be provided as freeze dried powder, which will be reconstituted with sterile water for injection to a concentration of 100 mg/mL. For the lowest doses the 100 mg/mL solution will be diluted to 10 or 1 mg/mL. The placebo solution, Placebo (109-0012) 0 mg/mL, will be provided as liquid. The placebo solution will also be used as diluent for the reconstituted active drug product. The freeze dried powder as well as the placebo solution should be kept at 2-8 °C. Both the trial drug and the placebo formulation will be administered subcutaneously, using standard syringes. Anti-IL-20 (109-0012) 100 mg/vial will be administered at the following doses (see also [Table 5-2](#)):

Single dose, dose-escalation phase: 0.01, 0.05, 0.20, 0.6, 1.5 and 3.0.

Multiple dose, dose-escalation phase: 0.05, 0.20, 0.5, 1.0 and 2.0.

| Visit number                        | 1            | 2   | 3 | 4 | 5  | 6   | 7   | 8   | 9   | 10  | 11  |
|-------------------------------------|--------------|-----|---|---|----|-----|-----------------|-----|-----------------|-----|-----|
| Timing: weeks                       | 0            | 1   |   | 2 | 3  | 5   | 7               | 9   | 11              | 13  | 16  |
| Timing: days                        | 0            | 1-2 | 3 | 8 | 15 | 29  | 43  | 57  | 71  | 85  | 106 |
| Window: days                        | -21
to -4 |     |   |   |    | ± 3 | ± 3             | ± 3 | ± 3             | ± 3 | ± 3 |
| Subject related
info/assessments |              |     |   |   |    |     |                 |     |                 |     |     |
| Informed consent                    | x            |     |   |   |    |     |                 |     |                 |     |     |
| Administration of trial product     |              | x   |   |   |    |     |                 |     |                 |     |     |

: Only telephone contact, no visit at site.

: Including known history of human immunodeficiency virus (HIV).

: Weight only.

: PK sampling of 109-0012 will occur prior to dosing (0 hours) and at 2, 4, 8, 10 and 24 hours after drug administration.

: Assessments will be performed prior to dosing on day 1, and 24 hours post-dosing.

: Sampling will occur prior to dosing (0 hours).

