## 5.4 Rationale for treatment

The trial drug is a protein and can therefore not be administered orally. A subcutaneous injection in the abdomen has been chosen as the most appropriate administration. During the trial, medical personnel will perform the injection. Due to risk for unblinding, the person performing the injection must be trial independent and not take part in any other trial related activities.

The first dose has been selected based on results from pre-clinical studies and biomodelling/simulation data. The expected dose range is between 0.01 mg/kg and 3 mg/kg during the SD phase, and between 0.05 mg/kg and 2 mg/kg during the MD dose-escalation phase. Initiation of the MD expansion phase, at the maximum tolerated dose, will depend on results from the dose-escalation phases and will be decided upon when the SD and MD dose-escalation phases have been completed. It will only be initiated as long as there is an acceptable safety profile. There will also be the possibility to go directly into a phase 2 dose-finding trial, and refrain from the MD expansion phase, provided there is an acceptable effect. The decision whether or not to continue with the MD expansion phase will be taken based on unblinded safety and efficacy data.

During the MD dose-escalation phase and the expansion phase four repeated doses, once every second week, will be investigated. This dosing interval is chosen with respect to the expected half-life of the trial drug and future dosing convenience for subjects.

The decision for dose-escalation will be taken by the Study Safety Group according to the instructions in [Table 5-2](#). Administration of Anti-IL-20 (109-0012) 100 mg/vial at the next dose level can only be initiated when the following criteria are met:

- Safety assessments and evaluations by the Study Safety Group through trial Day 15 for individual subjects in the current dose cohort of the SD dose-escalation phase, and through trial Day 57 of the MD dose-escalation phase.
- Evaluation of PK data by the Study Safety Group through trial Day 15 for individual subjects in the current dose cohort of the SD dose-escalation phase, and through trial Day 57 of the MD dose-escalation phase.

- The next dose level has been approved by the Study Safety Group. The Study Safety Group will also have the mandate to add another cohort other than for safety reasons, if relevant.

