3. ECG
4. BSA
5. PGA
6. PASI and VAS (if applicable)
7. Haematology
8. Biochemistry
9. Urinalysis
10. Hormones
11. Lipids
12. Sampling for molecular biomarkers (baseline)
13. Sampling for serum/plasma biomarkers (baseline)
14. Sampling for antibodies (baseline)
15. Blood sampling for genotyping

16. Lesional skin biopsies (1x6 mm to be split for histopathology+IHC and array/qRT-PCR analyses) and non-lesional skin biopsies (1x3 mm for baseline histopathology+IHC). This procedure is optional.
17. Urine pregnancy test (if applicable)
18. Inclusion and exclusion criteria
19. Quality of life questionnaire
20. Concomitant medication
21. Adverse events
22. PK sample (0 hours)

Thereafter subjects will be randomised **by IVRS** and receive a subcutaneous injection of either active treatment or placebo into the abdomen. Since the trial is double-blind, neither the subject nor the investigator/study nurse will know whether active treatment or placebo is administered. There is a 2:1 chance of receiving active treatment.

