## 9 Trial supplies

### 9.1 Trial products

The following trial products will be supplied by Novo Nordisk A/S:

- Anti-IL-20 (109-0012) 100 mg/vial as sterile freeze-dried powder in single use vials containing 127.5 mg drug substance. One 9 mL powder-containing vial is to be reconstituted with 1.1 mL of sterile Water for Injection, in order to obtain a concentration of 100 mg/mL.
- Placebo solution (Placebo (109-0012) 0 mg/mL) in single use vials containing 9 mL.
- Diluent solution (Placebo (109-0012) 0 mg/mL) in single use vials containing 9 mL to be used for preparation of single use vials of 10 mg/mL and 1 mg/mL strength solutions of 109-0012 for the dose-escalation phases.

The reconstituted Anti-IL-20 (109-0012) 100 mg/vial, as well as the Placebo (109-0012) 0 mg/mL, are colourless/almost clear solutions with pH of 6.5. It is recommended to use the trial drug immediately following reconstitution. The reconstituted preparations should be transferred to the dosing syringe no earlier than 1 hour prior to trial drug administration and stored below 25 °C (no freezing).

Detailed instructions regarding reconstitutions and dilution will be given in the Trial Materials Manual (TMM).

Appropriate volumes of Anti-IL-20 (109-0012) 100 mg/vial or Placebo (109-0012) 0 mg/mL will be administered, based on weight, as subcutaneous injections into the abdomen using a proper syringe. Please see the TMM for details.

The trial products are produced according to Good Manufacturing Practice. A TMM, detailing instructions on storage, handling and administration of the trial products, will be provided by Novo Nordisk. No trial product may be dispensed to any person except to the subjects enrolled into the trial.

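### The protocol says the subject will not know the treatment, yet states no means of hiding the syringe contents at the higher doses, where it concedes that active might differ in colour from placebo

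*Protocol*

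**What the plan says.** **Appearance.** Section 5.3 says the placebo "will have an identical appearance as the reconstituted freeze dried active drug at the lowest doses", and then: "At the higher doses the reconstituted active drug solution might differ in colour due to high protein content". Section 9.1 says that the reconstituted active product and the placebo alike "are colourless/almost clear solutions with pH of 6.5".

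**Strength.** Under section 5.3 the 100 mg/mL solution is "further diluted with the placebo formulation to 10 or 1 mg/mL for the lowest doses". Section 9.1 lists the diluent, and the two weaker strengths made with it, for the dose-escalation phases only. The expansion phase is run at the maximum tolerated dose (sections 5.1 and 5.3).

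**Device.** The Summary, under Trial products, says: "Both the trial drug and the placebo formulation will be administered subcutaneously, using standard syringes". Section 5.3 also names a standard syringe, with injection into the abdomen. Section 9.1 asks only for a suitable syringe and refers to the Trial Materials Manual for details. Section 8.5 mentions syringes without describing them.

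**Blinding.** Section 5.4 says: "Due to risk for unblinding, the person performing the injection must be trial independent". Sections 8.5 and 10.1 add an independent pharmacist or coordinator who fills the syringes, and section 10.1 gives the purpose as keeping the site staff blinded. Section 8.1.3, for the expansion phase, says that "neither the subject nor the investigator/study nurse will know whether active treatment or placebo is administered".

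**The concern.** The protocol claims double-blinding, admits a possible visible difference between the products, and deals with that difference only on the staff side. The subject is the other blinded party. A subject who receives an injection from an ordinary syringe may see its contents.

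The conceded difference belongs to the higher doses, and the expansion phase is placed at the top of the tolerated range. It is also the phase with the powered comparison of active with placebo. A subject who forms a view of the assigned arm could rate joint pain, quality of life or injection-site symptoms differently. The subject could also comment to the assessor, change use of the permitted creams, or leave the trial. None of this can be undone in the analysis.

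**Working it through.** The plan gives no figure for blinding, so the main check sets the passages side by side, with arithmetic on the strength in use.

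**1. Do the appearance statements agree?** Section 9.1 describes product reconstituted to 100 mg/mL, the undiluted strength, and calls it colourless or almost clear like placebo. Section 5.3 limits the match to the lowest doses and foresees a possible colour difference above them because of protein content. As written, the two do not fit together.

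**2. Which strength would the expansion phase use?** Inputs: strengths 10 and 100 mg/mL and a limit of 1.2 mL per injection (section 5.3); upper multiple-dose levels 0.5, 1.0 and 2.0 mg/kg (Table 5–1). Body weight of 60 to 120 kg is my assumption.

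Volume = dose × weight / strength. Injections = volume / 1.2, rounded up.

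| Dose, mg/kg | At 10 mg/mL | Injections | At 100 mg/mL | Injections |
|---|---|---|---|---|
| 0.5 | 3.0–6.0 mL | 3–5 | 0.3–0.6 mL | 1 |
| 1.0 | 6.0–12.0 mL | 5–10 | 0.6–1.2 mL | 1 |
| 2.0 | 12.0–24.0 mL | 10–20 | 1.2–2.4 mL | 1–2 |

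The upper levels are in practice undiluted, which agrees with section 9.1 listing dilutions only for escalation. If escalation stopped early and the maximum tolerated dose were 0.05 or 0.20 mg/kg, a diluted strength would be feasible by volume (0.3–0.6 mL and 1.2–2.4 mL at 10 mg/mL), and the concern would weaken.

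**3. Whom do the safeguards cover?**

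| Person | Stated measure |
|---|---|
| Investigator, study nurse, assessor | Kept apart from preparation and injection (5.4, 8.5, 10.1) |
| Pharmacist, injector | Independent of other trial activities |
| Subject | None stated: no sleeve, opaque label, screen or colour-matched placebo at the higher doses |

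**4. How many occasions?** 39 subjects × 4 doses = 156 dosing visits in the expansion phase. One injection at 100 mg/mL holds at most 1.2 × 100 = 120 mg. At 2 mg/kg, subjects above 120 / 2 = 60 kg need more than one. The upper escalation levels share the exposure.

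**5. Which outcomes?** VAS is self-rated and applies only to subjects with psoriatic arthritis. If the 10–30% in section 3.1.1 applied here, that is 3.9 to 11.7 of 39 subjects. DLQI is a questionnaire, and itching, burning and pain at the injection site are reported by the subject. PASI and PGA are scored by staff.

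**6. Could the indirect route upset PASI75?** The stated power of 83% (26 + 13 subjects, 60% against 10%, two-sided Fisher's exact test, 5%) reproduces as 83.8% by exact enumeration when the two-sided p-value is twice the one-sided tail. It is 89.0% when tables of equal or lower probability are summed. The illustration below uses the second convention, no drug effect, and assumed response rates that are not in the documents:

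| Active / placebo PASI75 | Chance of rejection |
|---|---|
| 10% / 10% | 1.8% |
| 20% / 10% | 3.8% |
| 25% / 10% | 9.7% |
| 30% / 10% | 19.0% |

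A 10-point shift produced purely by guessing the arm would leave the error rate under 5%. A 15-point shift would not.

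**The case against.** The strongest reply is that a visible difference is not established. Section 5.3 says only that one might exist, and section 9.1 describes the two products in the same terms. Section 9.1 also sends administration details to the Trial Materials Manual, where a masking step could sit. Each subject takes part once and receives one product, so must recognise a slight tint with nothing to compare it with. The PASI and PGA scorers neither prepare nor inject.

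Most of this stands as a limit on strength. It rules out several readings that a reader might infer:

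- **That subjects will be unblinded.** The documents support a possible difference and no stated masking, not an observed failure. That the subject can see the syringe is itself an inference.
- **That seeing the product repeatedly measures unblinding.** The 156 visits and any second syringe count opportunities. They still offer no comparison with the other arm.
- **That the bias favours active.** A subject who suspects placebo and uses more of the permitted low-potency corticosteroid cream could improve the placebo result. Dropout has no fixed direction, and subjects leaving before Day 57 are to be replaced (section 6.5).
- **That the 3 mg/kg volumes apply to the expansion phase.** That level is a single dose; the highest planned multiple dose is 2 mg/kg.

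The reply does not remove the gap. The protocol recognises a risk of unblinding, names an ordinary syringe in two places, and states a remedy for staff only. A reader who follows the text as written has no instruction that supports the claim about the subject.

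**Conclusion.** The point holds as a cheap improvement. Sections 5.3 and 9.1 disagree on appearance, and subject blinding at the undiluted strength is asserted without a stated means. The expansion phase is where this matters most, with up to 39 subjects and 156 dosing visits.

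The direct risk is to VAS, DLQI and injection-site symptoms. These are secondary or descriptive, although VAS is also named in the expansion phase's primary objective (section 4.1). PASI75 is exposed only through remarks to the assessor, cream use and dropout. The size and direction of any bias cannot be derived from the documents.

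The conclusion assumes that the expansion phase takes place, that its dose is high enough to need undiluted product, and that the Trial Materials Manual does not already require masking.

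**What to change.** - In the Summary (Trial products) and section 5.3, replace the standard syringe with one masked by an opaque sleeve or label, identical in both arms and at all dose levels. The unblinded pharmacist applies it after verifying the volume.
- Add the same requirement to sections 8.5 and 9.1, which do not now describe the device, and carry it into the Trial Materials Manual. If the manual already has such a step, state it in the protocol and cross-refer.
- Reconcile the appearance statements in sections 5.3 and 9.1 so that they say the same about the undiluted product.

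Cost: sleeves or labels and a few lines of text, with no added visits, subjects or staff. The one drawback is that the injector cannot read the volume through the mask, so the pharmacist's check beforehand must be mandatory.

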**Table 5–1 Dose levels for the SD and MD dose-escalation phases and proposed initiation times.**

| Time when the different dose levels will be started (weeks) | SD, mg/kg                     | MD, mg/kg
(accumulated doses after four administrations) |
|-------------------------------------------------------------|-------------------------------|-------------------------------------------------------------|
| FPFV (W 0) to LPLV (W 55)                                   | Maximum dose level
3 mg/kg | Maximum dose level
2 mg/kg                               |
| W* 0                                                        | Level 1: 0.01                 |                                                             |
| W 5                                                         | Level 2: 0.05                 |                                                             |
| W 10                                                        | Level 3: 0.20                 |                                                             |
| W 15                                                        | Level 4: 0.6                  | Level 1: 0.05 (0.2)                                         |
| W 20                                                        | Level 5: 1.5                  |                                                             |
| W 25                                                        | Level 6: 3.0                  | Level 2: 0.20 (0.8)                                         |
| W 35                                                        |                               | Level 3: 0.5 (2.0)                                          |
| W 45                                                        |                               | Level 4: 1.0 (4.0)                                          |
| W 55                                                        |                               | Level 5: 2.0 (8.0)                                          |
| LPLV: W 77                                                  |                               |                                                             |

\* Related to the dosing of the first subject in the trial, and not to trial Week of each individual subject.

Dosing will occur every second week during the MD phases (dose-escalation and expansion phase), for a total of four doses. All subjects will be followed for 16 weeks after last dose and with a

suggested half-life of about 15-20 days the drug is then anticipated to have been sufficiently cleared from the body.

Other anti-psoriatic treatments, except moisturising cream and low potency corticosteroid cream (group 1), will not be allowed during the trial. For more specific details regarding prohibited concomitant medication see section [6.3](#).

## 5.4 Rationale for treatment

The trial drug is a protein and can therefore not be administered orally. A subcutaneous injection in the abdomen has been chosen as the most appropriate administration. During the trial, medical personnel will perform the injection. Due to risk for unblinding, the person performing the injection must be trial independent and not take part in any other trial related activities.

The first dose has been selected based on results from pre-clinical studies and biomodelling/simulation data. The expected dose range is between 0.01 mg/kg and 3 mg/kg during the SD phase, and between 0.05 mg/kg and 2 mg/kg during the MD dose-escalation phase. Initiation of the MD expansion phase, at the maximum tolerated dose, will depend on results from the dose-escalation phases and will be decided upon when the SD and MD dose-escalation phases have been completed. It will only be initiated as long as there is an acceptable safety profile. There will also be the possibility to go directly into a phase 2 dose-finding trial, and refrain from the MD expansion phase, provided there is an acceptable effect. The decision whether or not to continue with the MD expansion phase will be taken based on unblinded safety and efficacy data.

During the MD dose-escalation phase and the expansion phase four repeated doses, once every second week, will be investigated. This dosing interval is chosen with respect to the expected half-life of the trial drug and future dosing convenience for subjects.

The decision for dose-escalation will be taken by the Study Safety Group according to the instructions in [Table 5-2](#). Administration of Anti-IL-20 (109-0012) 100 mg/vial at the next dose level can only be initiated when the following criteria are met:

- Safety assessments and evaluations by the Study Safety Group through trial Day 15 for individual subjects in the current dose cohort of the SD dose-escalation phase, and through trial Day 57 of the MD dose-escalation phase.
- Evaluation of PK data by the Study Safety Group through trial Day 15 for individual subjects in the current dose cohort of the SD dose-escalation phase, and through trial Day 57 of the MD dose-escalation phase.

- The next dose level has been approved by the Study Safety Group. The Study Safety Group will also have the mandate to add another cohort other than for safety reasons, if relevant.

**Table 5–2 Dose-escalation rules**

| Number of subjects with grade 3 toxicity (CTCAE) related to trial product administration | Decision rules                                                                                                                                                                                                                                                                                                                                                                                                                                                                                                                                                                                                                  |
|------------------------------------------------------------------------------------------|---------------------------------------------------------------------------------------------------------------------------------------------------------------------------------------------------------------------------------------------------------------------------------------------------------------------------------------------------------------------------------------------------------------------------------------------------------------------------------------------------------------------------------------------------------------------------------------------------------------------------------|
| 0                                                                                        | Enter four subjects (3+1) at the next dose level, according to Table 5–1 .                                                                                                                                                                                                                                                                                                                                                                                                                                                                                                                                      |
| 1 of 4                                                                                   | Enter four subjects (3+1) at the same dose level as the current level where the toxicity event occurred.                                                                                                                                                                                                                                                                                                                                                                                                                                                                                                                        |
| 1 of 8                                                                                   | Enter four subjects (3+1) at the next dose level, according to Table 5–1 .                                                                                                                                                                                                                                                                                                                                                                                                                                                                                                                                      |
| ≥2                                                                                       | 
The dose-escalation will be stopped at this level, and no further increase of dose will occur. There will however be the possibility to add four (3+1) subjects at one or maximally two different dose levels between the current dose limiting level and the previous dose level.
 
 
• The maximum tolerated dose (MTD) is the highest dose level below the maximum administered dose (MAD) where none or 1 subjects experience a DLT.
 
• The maximum administered dose is the highest dose given in the trial.
 
• The maximal feasible dose is 3 mg/kg.
 
 |

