### Severity assessment

The National Cancer Institute's (NCI) Common Terminology Criteria for Adverse Events (CTCAE) Version 3.0 will be used to assess and grade severity for adverse events and for laboratory abnormalities judged to be clinically significant.

The CTCAE Version 3.0 is a descriptive terminology with a grading (severity) scale provided for each AE term. Within each category, AEs are listed accompanied by their descriptions of severity (Grade 1-5). Each AE term will be mapped to a MedDRA term and code. For this trial the CTCAE will only be used for grading the severity of an AE and not for causality assessment.

If the event is not covered in CTCAE Version 3.0, the guidelines shown in [Table 12-1](#) should be used to assess severity.

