#### 12.1.1 Definition of dose limiting toxicities

Grade 3 AEs or higher will represent Dose Limiting Toxicities (DLT), except when the relationship to trial product is judged as unlikely.

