#### MD, dose-escalation phase

The safety summary report for the decision on dose-escalation in the MD dose-escalation phase will contain information on laboratory safety data, AEs including local tolerability, vital signs, ECG evaluations and subject related information for all subjects in the dose cohort through trial Day 57, as well as PK data through trial Day 57. PK data will be presented in such a manner that unblinding of the Safety Group is avoided.

Sites must not proceed to the next dose level with the new dose cohort before the recommendation from the Novo Nordisk Study Safety Group to escalate has been issued. The Study Safety Group can also recommend to stop further dose-escalations, or to add another cohort (N=3+1) of patients to the last performed dose cohort based on safety (see [Table 5-2](#)) or due to inconclusive PK and/or clinical data. Dose cohorts in-between existing dose levels can also be added (see [Table 5-2](#)). Maximally 8 subjects can be treated at the same dose level.

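### The escalation table counts only grade 3 related toxicity, so read literally a related grade 4 or 5 event leaves the count at zero and the table says to go up a dose

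*Protocol*

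**What the plan says.** Protocol section 5.4 makes the table operative: "The decision for dose-escalation will be taken by the Study Safety Group according to the instructions in" Table 5–2. The row is chosen by the "Number of subjects with grade 3 toxicity (CTCAE) related to trial product administration". The rows are:

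- **0:** "Enter four subjects (3+1) at the next dose level, according to" Table 5–1.
- **1 of 4:** treat a second cohort of 3+1 at the same level.
- **1 of 8:** go to the next level.
- **2 or more:** stop escalating, with the option of intermediate levels.

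The last row also defines the MTD as the highest level below the maximum administered dose "where none or 1 subjects experience a DLT"; section 12.1.2 repeats this. Section 12.1.1 supplies the DLT definition: "Grade 3 AEs or higher will represent Dose Limiting Toxicities (DLT), except when the relationship to trial product is judged as unlikely".

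Section 12.1 (Severity assessment) grades events on the CTCAE scale from 1 to 5. Table 12–1, used for events that CTCAE does not cover, gives severe, life-threatening and fatal events separate grades 3, 4 and 5.

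**The concern.** Two event definitions operate in one table. The count that drives repeat, escalate and stop is grade 3; the MTD criterion uses grade 3 or higher. Nothing in the protocol extends the count to grades 4 and 5, and section 12.1.1 shows that the protocol writes *or higher* where it means it.

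The written rule therefore leaves out the life-threatening and fatal related events, which most need to be in it. The trial is the first use of this antibody in humans, and section 5.2 says the starting dose could not be based on the minimal anticipated biological effect level. A numeric escalation rule there should not depend on readers silently correcting its heading.

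**Working it through.** **1. The text applied to the same data.** The protocol states no operating characteristics for the rule, so there is no figure to reproduce. The comparison uses related events only:

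| Subjects in a cohort of 4 | Count as written | Table 5–2 says | DLT count (12.1.1) | The same rows would say |
|---|---|---|---|---|
| one grade 3 | 1 | repeat level | 1 | repeat level |
| one grade 4 or 5 | 0 | next level | 1 | repeat level |
| two grade 4 or 5 | 0 | next level | 2 | stop |
| one grade 3 and one grade 4 or 5 | 1 | repeat level | 2 | stop |

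In the third line the table says to escalate from a level that fails the MTD criterion of at most one DLT subject. In the fourth line the same happens if the repeat cohort adds no grade 3 event (1 of 8). A single grade 4 or 5 event at a level does not cause this clash with the MTD.

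**2. Illustration of size.** Assumptions, none of them from the protocol: a per-subject DLT rate p of 5%, 10%, 20% or 33% on active drug; no events on placebo; the table followed mechanically. The 3 active subjects per cohort come from the protocol.

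Let q be the per-subject rate of events that the table counts. Then

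P(table says next level) = P(0 of 3) + P(1 of 3) × P(0 of 3) = (1−q)³ + 3q(1−q)² × (1−q)³.

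Example at q = 0.20: 0.512 + 0.384 × 0.512 = 0.709.

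| DLT rate p | DLTs counted (q = p) | As written, half of DLTs grade 4–5 (q = p/2) | As written, all grade 4–5 (q = 0) |
|---|---|---|---|
| 5% | 0.973 | 0.993 | 1.000 |
| 10% | 0.906 | 0.973 | 1.000 |
| 20% | 0.709 | 0.906 | 1.000 |
| 33% | 0.434 | 0.783 | 1.000 |

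**3. How often the instruction would clash with the MTD criterion.** This is the probability that the table says next level although two or more subjects at that level have a DLT. If all DLTs are grade 4–5, no second cohort is ever triggered and the probability is 3p²(1−p) + p³. At p = 0.20 that is 0.096 + 0.008 = 0.104. If half are grade 4–5, it comes from enumerating all outcomes, including those of the second cohort.

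| DLT rate p | DLTs counted | Half grade 4–5 | All grade 4–5 |
|---|---|---|---|
| 5% | 0 | 0.010 | 0.007 |
| 10% | 0 | 0.034 | 0.028 |
| 20% | 0 | 0.104 | 0.104 |
| 33% | 0 | 0.193 | 0.255 |

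**The case against.** The strongest reply is that nobody would read the heading that way. The last row of the table speaks of a dose limiting level and uses the term DLT, so grade 3 is naturally taken as a threshold. That is very likely the intent.

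Nor is a count of 0 sufficient on its own. Section 5.4 lists as a condition for moving up that "The next dose level has been approved by the Study Safety Group", after review of the safety data. Section 12.6.1 asks the Group to evaluate all safety data, bars sites from proceeding before its recommendation, and adds for the multiple dose phase that "The Study Safety Group can also recommend to stop further dose-escalations". Life-threatening and fatal events are also serious adverse events reportable within 24 hours, and the sponsor, an investigator or a regulator may stop the trial at any time. The MTD definition already counts DLTs, so a level with two or more DLT subjects cannot be named the MTD.

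All of this stands, and it makes actual escalation after a related grade 4 or 5 event unlikely. It does not correct the rule. Section 5.4 authorises the Group to withhold approval, but doing so after such an event gives a different result from the row that the Group is told to apply. No numeric rule then says whether to repeat the level or stop.

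It is also fair that the probabilities describe the table without the Group, that the value of 1.00 follows directly from q = 0, and that the largest contrasts need a 33% DLT rate with every DLT grade 4 or 5. The point does not rest on them.

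**Conclusion.** The concern holds. The heading of Table 5–2 is wrong as written: it is inconsistent with section 12.1.1 and with the MTD bullet in the table itself, and no other text repairs it. This is a mismatch of wording in a rule that governs safety, most likely unintended, and not evidence that the sponsor means to escalate after grade 4 or 5 events.

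How far the written rule is too permissive depends on the unknown share of DLTs that are grade 4–5. At an assumed 20% DLT rate, the probability of an instruction to escalate rises from 0.71 to 0.91 if that share is half and to 1.00 if it is all. These are probabilities of the table's instruction, not of actual escalation, which needs the Study Safety Group's approval. The mismatch itself needs no assumption. It should be fixed; confidence in the textual finding is high.

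**What to change.** Replace the column heading with: *Number of subjects with a DLT (CTCAE grade 3 or higher, possibly or probably related; see 12.1.1)*. The two relationship categories are those that section 12.1 leaves once unlikely is excluded. One definition then drives repeating, escalating, stopping and the MTD.

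The cost is one table heading. Visits, cohort sizes and trial conduct do not change.
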